#### Group Reminiscence (Remembering Yesterday, Caring Today)

The group reminiscence intervention follows the RYCT programme for people with dementia and their family carers [17]. Twelve weekly sessions, each lasting two hours, cover a range of themes including: childhood and family life; school days; courting and marriage; food and cooking; and the next generation. Each session explores its theme using multisensory triggers and activities, including group discussions, small group activity, object handling, enacting or improvisation, and singing songs. The RYCT intervention is provided by either the NHS host organisation or the host voluntary sector organisation depending on usual practice in each locality. The SHIELD programme runs RYCT in community settings such as church halls, with transport provided if needed. Each group session is led by two experienced Facilitators, supported by a team, including volunteers, health and social care staff and trainees to facilitate small group discussion and activities and engage the people with dementia. All members of the RYCT team must attend a training day led by one of the original RYCT programme authors.

During four of the sessions, the family carers meet together with one of the Facilitators and another team member for about 45 minutes, whilst the other Facilitator and remaining team work with the people who have dementia. The Carers' sessions aim to develop listening and communication skills and consider how the activities and strategies used within the sessions can be carried over into the home environment. After the 12 initial sessions, monthly reunion sessions take place over a further seven months using previously successful themes, or using new themes, depending on the preferences of the group.

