### Sample size

We based sample size calculations on the BECCA [12] and REMCARE [18] trials. These predicted effect sizes, defined as average effect per participant divided by population standard deviation, of 0.42 for CSP and 0.35 for RYCT. In a 2 × 2 factorial design using a 2:1 allocation ratio in favour of groups receiving RYCT, a completed sample of 240 dyads would yield power of more than 90% to detect both main effects using a significance level of 5%. This design would also yield power of more than 80% to detect interaction between CSP and RYCT equivalent to an effect size of 0.4, using an analogous definition. As both the REMCARE trial platform and BECCA retained some 80% of participants, we aim to recruit 300 dyads in 13 rounds of 24 dyads to yield a final sample of 240 dyads.

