### Randomisation

We use a two-stage sequential dynamic algorithm to allocate individual and group based interventions. We base the probability of choosing each group on the participants' stratification variables and the previous allocations for those variables. For the first allocation between CSP and TAU the stratification variables are locality and dyad relationship. In the latter, dyads are designated 'horizontal' or 'vertical' kinship, where horizontal denotes spouses and siblings and vertical denotes daughters, sons, daughters-in-law and other similar kinships where there carer and person with dementia are from different generations within the family. For the second allocation between RYCT and TAU we add the first allocation as a stratification variable to keep the four treatment arms in balance.

The SHIELD administrator enters participants' variables into a remote web-based randomisation, which then allocates them in equal proportions between CSP or TAU on an individual basis. Once adequate dyads have been randomised within each site (target 24; range 16-30), the remote randomisation system allocates them in a second randomisation between RYCT and TAU in the proportion 2:1 on a group basis. Hence the combination of these two randomisation stages results in results in the allocation between TAU, RYCT, CSP, and RYCT plus CSP in the proportions 1:2:1:2. The (unblinded) SHIELD administrator then informs carers of their allocation by letter, and liaises with the RYCT Facilitator and/or CS Coordinator as appropriate.

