#### Effectiveness analysis

After exporting data to the statistical package SPSS, we shall follow the general approach of the UK BEAM trial [51] and analyse relevant outcomes on the basis of treatment allocated to test whether:

A. CSP, alone or in combination with RYCT, affected family carers and their relatives;

B. RYCT, alone or in combination with CSP, affected family carers and their relatives;

C. CSP and RYCT interacted in their effects on these outcomes.

Specifically we shall use multi-level analysis of covariance with outcome at 12 months after initial randomisation as dependent variable and 'outcome' at baseline and length of time on CSP as covariates, to compare: (A) CSP and combined groups with TAU and RYCT groups; (B) RYCT and combined groups with TAU and CSP groups; and (C) combined and TAU groups with CSP and RYCT groups. We shall also use linear mixed models to study longitudinal effects at 5 and 12 months. We shall treat RYCT versus TAU and CSP versus TAU as fixed effects, together with gender and dyad relationship. We shall treat the effects of locality (including personnel) and time as random effects and assess the covariance structure of this. We shall undertake sensitivity analysis to test whether plausible changes in key variables such as carers' ages and relationships to their relatives with dementia would have affected findings.

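### RYCT is delivered in groups, but the sample size and the named random effects leave the group out, so the RYCT main effect may be reported too precisely

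*Protocol article*

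**What the plan says.** **Delivery.** RYCT consists of twelve weekly two-hour sessions followed by seven months of monthly reunions. Under Group Reminiscence the article says "Each group session is led by two experienced Facilitators", supported by a team.

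**Formation of groups.** Under Randomisation, the RYCT allocation waits for a batch: "Once adequate dyads have been randomised within each site (target 24; range 16-30"). The batch is then split 2:1 between RYCT and treatment as usual (TAU). Under Sample size: "we aim to recruit 300 dyads in 13 rounds of 24 dyads to yield a final sample of 240 dyads".

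**Power.** The predicted effect sizes are "of 0.42 for CSP and 0.35 for RYCT", "defined as average effect per participant divided by population standard deviation". The claim is that "a completed sample of 240 dyads would yield power of more than 90% to detect both main effects". The paragraph contains no ICC, group size or design effect.

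**Analysis.** Effectiveness analysis specifies a multi-level analysis of covariance at 12 months without naming its levels. It then adds linear mixed models for 5 and 12 months, and states: "We shall treat the effects of locality (including personnel) and time as random effects". The RYCT group is not named as a level or random effect anywhere in the article.

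**The concern.** Dyads in the same RYCT group share facilitators, sessions and one another's company for about ten months. Their outcomes may be more alike than those of dyads in different groups. This dependence is created by the intervention, so it exists only in the RYCT-alone and combined arms.

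The random effects that are named do not capture it. There are four localities, against about 13 groups. Each locality also contains dyads with and without RYCT, so a locality intercept is common to both sides of the comparison. It cannot absorb variation that exists only on the RYCT side.

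At stake is the comparison of the RYCT and combined arms with the TAU and CSP arms. That comparison tests one of the trial's three null hypotheses on the primary outcome. The RYCT cost-effectiveness result has the same exposure, because the planned bootstrap resamples dyads and preserves only the sizes of the four arms.

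**Working it through.** **Inputs from the article.** 240 completed dyads; 2:1 for RYCT, so 160 v 80; 1:1 for CSP, so 120 v 120; effect sizes 0.35 and 0.42 with SD = 1; 5% significance, taken as two-sided; 13 rounds; four localities.

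**Assumptions, not in the article.** ICC of 0.01 to 0.10 in the RYCT arms; one RYCT group per round, so m = 160/13 = 12.3 completers; no baseline-covariate gain unless stated.

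**Step 1: the stated power, without clustering.** Power = Φ(d/SE − 1.96).
- CSP: SE = √(1/120 + 1/120) = 0.1291; Φ(0.42/0.1291 − 1.96) = 90.2%. This reproduces.
- RYCT: SE = √(1/160 + 1/80) = 0.1369; Φ(0.35/0.1369 − 1.96) = 72.4%. This does not reproduce a figure above 90%. A baseline correlation of about 0.615 would raise it to 90%, since the SE is multiplied by √(1 − 0.615²); the article states no such correlation. This shortfall is a separate error.

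**Step 2: add the RYCT group.** DE = 1 + (m − 1) × ICC applies to the RYCT arms only, so SE = √(DE/160 + 1/80). The type I error of the naive test is 2(1 − Φ(1.96 × 0.1369/SE)).

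| ICC | DE | SE | SE v naive | Type I error | Power, no covariate | Power, r = 0.615 |
|---|---|---|---|---|---|---|
| 0 | 1.00 | 0.1369 | – | 5.0% | 72.4% | 90.0% |
| 0.01 | 1.11 | 0.1395 | +2% | 5.4% | 70.9% | 88.9% |
| 0.02 | 1.23 | 0.1420 | +4% | 5.9% | 69.3% | 87.8% |
| 0.05 | 1.57 | 0.1493 | +9% | 7.2% | 65.0% | 84.5% |
| 0.10 | 2.13 | 0.1607 | +17% | 9.5% | 58.6% | 78.9% |

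For example, at ICC 0.05: DE = 1 + 11.3 × 0.05 = 1.57; SE = √(1.57/160 + 0.0125) = 0.1493; 0.1493/0.1369 = 1.09.

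**Step 3: sensitivity to group size.** If each round formed two groups, m = 160/26 = 6.2. At ICC 0.02, 0.05 and 0.10 the SE rises by 1.7%, 4.2% and 8.2%, and type I error is 5.4%, 6.0% and 7.0%. That is about half the SE inflation.

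**Step 4: does locality in the model help, and which contrasts are affected?** Simulation: 20,000 runs per ICC, 13 groups in four localities, combined and RYCT-alone dyads sharing groups. The model had locality, CSP, RYCT and their interaction, with no group term. Rejection rates under the null:

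| ICC | RYCT | CSP | Interaction |
|---|---|---|---|
| 0.01 | 5.5% | 5.0% | 5.1% |
| 0.02 | 5.8% | 4.7% | 4.9% |
| 0.05 | 7.4% | 4.8% | 5.1% |
| 0.10 | 9.3% | 4.9% | 5.0% |

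Adjusting for locality leaves the RYCT inflation in place. CSP and the interaction are unaffected because CSP is balanced within each RYCT group, so a shared group effect cancels.

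**The case against.** **The random-effects sentence may not govern the main analysis.** It follows the description of the longitudinal models, and a random time effect has no role in a single-time-point analysis. The main analysis is called multi-level, and a fuller plan could name the group as a level. This stands as a reason for caution. However, the article builds group formation into its randomisation, names specific random effects, and includes the group neither there nor in the sample size.

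**Personnel are mentioned, and the covariance structure will be assessed.** This shows that some clustering was considered. It does not separate about 13 groups within four localities, nor confine the effect to the RYCT arms.

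**The size rests on assumptions.** This stands. The article gives no ICC and does not say that each round forms exactly one group. At ICC 0.01 the effect is small.

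**Stronger readings that a reader might infer, and that the article does not support:**
- That the CSP and interaction tests are also anti-conservative. CSP is allocated individually, and nothing suggests that combined and RYCT-alone dyads attend separate groups. With shared groups, neither test is inflated.
- That clustering explains the gap between the stated power and 59% to 71%. Most of that gap is present at ICC 0. Clustering itself costs about 1.5, 3, 7 and 14 percentage points across the ICC range.
- That the longitudinal model cannot give separate effects at 5 and 12 months because no allocation-by-time term is listed. The list is condensed: it also omits the interaction and baseline score that the same section says will be used.

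**Conclusion.** The concern holds for the RYCT main effect, conditional on positive correlation within RYCT groups. With one group per round and an ICC of 0.01 to 0.10, the reported standard error would be about 2% to 17% too small, and the type I error about 5.4% to 9.5%. With more than one group per round the effect is smaller.

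RYCT power is lowered as well, to between 70.9% and 58.6% without a covariate gain, or between 88.9% and 78.9% with an assumed baseline correlation of 0.615. This comes on top of the separate arithmetic shortfall. The calculations read the second allocation as splitting dyads 2:1 within each batch, which fits the use of the first allocation as a stratification variable.

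The point goes beyond missing detail: the design creates a known source of dependence, and the stated sample size and random effects both leave it out.

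**What to change.** 1. In the 12-month analysis of covariance and the longitudinal model, add a random effect for RYCT group that is present only in the RYCT-alone and combined arms (a partially nested model). Use small-sample degrees of freedom, since there are only about 13 groups.
2. When bootstrapping net benefit for RYCT, respect group membership in the RYCT arms rather than resampling dyads as if independent.
3. Restate RYCT power with an explicit ICC range, the expected number of completers per group, and any baseline correlation relied on. Show the clustering loss separately from the correction of the unclustered figure.
4. State how many RYCT groups each round forms, and that combined and RYCT-alone dyads attend the same groups, if so.

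The cost is wording and some programming. No new outcome data are needed, and group membership arises from allocation and delivery. The price is slightly wider RYCT confidence intervals and a lower stated RYCT power. The change should be fixed before unblinded analysis.

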#### Cost-effectiveness analysis

The primary health economic evaluation will estimate the incremental cost-effectiveness of:

A. CSP compared with TAU, both alone or both in combination with RYCT;

B. RYCT compared with TAU, both alone or both in combination with CSP;

C. CSP and RYCT combined compared with TAU.

These analyses will take a societal perspective, and measure effectiveness on the MCS-12 [28]. In principle each cost-effectiveness analysis will have five stages: (a) measurement of outcomes; (b) measurement of costs; (c) estimation of incremental cost-effectiveness ratio (ICER); (d) calculation of net benefits and derivation of cost-effectiveness acceptability curve (CEAC); (e) and sensitivity analyses. As these three analyses have many possible combinations of outcomes we shall follow the standard economic evaluation approach of extended dominance.

#### Outcome estimation

The economic evaluation will employ the same procedures for calculating scores and imputing missing values as in the primary statistical analyses described above.

#### Cost estimation

The economic evaluation will use responses on the validated CSRI [48] completed with the carer. We will attach nationally relevant unit costs to services used by participants, using the most recent Personal Social Services Research Unit 'Unit Costs' volume where available [52], and costed locally where not, for example for CSP and RYCT. The time inputs of carers and their lost productivity (from giving up or reducing employment) will be costed using a range of methods to reflect the opportunity costs to those individuals, and the consequences of differences explored in sensitivity analyses. The primary economic analysis will include costs, both of service use and of carer inputs (a societal perspective).

We shall compare the outcomes and costs of the four allocated groups. For example, we shall interpret CSP as more cost-effective than TAU (both alone or both in combination with RYCT) if: (i) it is both less costly and more effective on the MCS-12; or (ii) it is both more costly and more effective, and the decision maker values the improvement in outcome at more than the additional cost; or (iii) it is both less costly and less effective and the decision-maker attaches lower value to the loss of outcome than the cost savings. In the fourth option, when CSP is more costly and less effective than TAU, the decision maker-would prefer TAU.

To quantify options (ii) and (iii) in this example, we shall estimate the ICER, namely the mean cost difference between CSP and TAU (both alone or both in combination with RYCT) over the follow-up period of 12 months divided by the mean difference between these groups in the MCS-12 over those 12 months. We will also estimate net benefit (NB) for each dyad from the standard formula:

NB=λ×E-C

where:

E is effectiveness, namely the change in the primary outcome; C is the cost for that dyad (services used by the carer and the person with dementia, plus indirect costs of carer time); and λ is the decision-maker's willingness to pay for one additional unit of outcome. After calculating net benefits for each dyad for plausible values of λ, we shall address the expected skewness in the distribution of NBs by 'bootstrapping'; this is the technique of drawing (say) 10,000 independent replicates with replacement from the original sample of (say) 240 dyads while keeping the four allocated groups at their original sizes. For each value of λ we shall use these replicated samples to estimate the true proportion of dyads whose net benefit is positive, and derive a CEAC plotting the likelihood of CSP being cost-effective relative to TAU (both alone or both in combination with RYCT) against λ, the decision-maker's willingness to pay. We shall conduct sensitivity analyses to explore the effect on conclusions of varying key assumptions about costs and outcomes.

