#### Resource Use

The Client Service Receipt Inventory (CSRI) [48] is used to collect information retrospectively about use of health, social care and other relevant services, accommodation and living situation, benefits, carer support, and employment. It provides data from which we calculate costs.

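### The cost and net-benefit analysis, as described, has no baseline-cost term although the clinical analysis adjusts for baseline; the cost difference stays unbiased but loses precision

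*Protocol article*

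**What the plan says.** All references are to the protocol article.

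- **Cost estimation, ICER.** The numerator is "namely the mean cost difference between CSP and TAU (both alone or both in combination with RYCT) over the follow-up period of 12 months". The denominator is the mean difference in MCS-12. No covariate is named.
- **Cost estimation, net benefit.** For each dyad NB = λ×E − C. On the effect side, "E is effectiveness, namely the change in the primary outcome", so the baseline value enters. C is the dyad's own cost of services and carer time, with no baseline term.
- **Cost estimation, bootstrap.** Replicates are drawn "with replacement from the original sample of (say) 240 dyads while keeping the four allocated groups at their original sizes". No model is fitted within a replicate.
- **Outcome estimation.** "The economic evaluation will employ the same procedures for calculating scores and imputing missing values as in the primary statistical analyses described above". Scoring and imputation carry over from the statistical analysis; covariate adjustment is not mentioned.
- **Effectiveness analysis.** The 12-month ANCOVA takes the baseline outcome as a covariate. The longitudinal mixed model includes dyad relationship as a fixed effect and locality as a random effect.
- **Randomisation.** "For the first allocation between CSP and TAU the stratification variables are locality and dyad relationship". The second allocation adds the first as a further stratifier.
- **Resource Use and Design.** The CSRI "is used to collect information retrospectively about use of health, social care and other relevant services". Trial data are collected at baseline, 5 and 12 months; no schedule or recall period is given for the CSRI itself.
- **Secondary cost-effectiveness analyses.** The same approach is repeated from the health and social care perspective and for QALYs.

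**The concern.** The trial treats its two halves differently. Clinical outcomes are adjusted for their baseline value, and E in the net benefit is a change from baseline. Only the cost term has no baseline counterpart, and no reason is given.

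Costs of dementia care are likely to be skewed and to persist within a dyad. If one arm happens to start with more high-cost dyads, part of that excess appears in the follow-up cost difference and moves the ICER. The bootstrap allows for this possibility, but by giving a wider spread than an adjusted analysis would need. The sample was sized on clinical effect sizes, with no target for cost, so nothing else in the design protects precision on the cost side. Because the secondary economic analyses repeat the approach, the choice affects every ICER and CEAC.

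**Working it through.** **Group sizes.** The Sample size section aims for 300 recruited and 80% retained: 300 × 0.80 = 240, which agrees with the stated figure. Allocation to TAU, RYCT, CSP and combined at 1:2:1:2 gives 40, 80, 40 and 80 dyads. The three comparisons listed under Cost-effectiveness analysis are then:

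- A (CSP): 120 v 120
- B (RYCT): 160 v 80
- C (combined v TAU): 80 v 40

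**Assumed input.** The documents give no cost SD and no correlation (ρ) between baseline and follow-up cost. Results are therefore in units of the cost SD, for ρ = 0.3, 0.5 and 0.7.

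**Formulae.**
- Unadjusted SE = √(1/n₁ + 1/n₂).
- SE adjusted for baseline cost = unadjusted SE × √(1 − ρ²). The factor is 0.954, 0.866 or 0.714, a reduction of 5%, 13% or 29%.
- The error carried by chance imbalance in baseline cost has SD = ρ × unadjusted SE; its 95% range is ±1.96 times that.

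**Results.**

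| Comparison | Unadjusted SE | Adjusted SE (ρ = 0.3 / 0.5 / 0.7) | Unadjusted 95% half-width | 95% range of error from baseline imbalance (ρ = 0.3 / 0.5 / 0.7) |
|---|---|---|---|---|
| A | 0.129 | 0.123 / 0.112 / 0.092 | 0.25 | ±0.08 / 0.13 / 0.18 |
| B | 0.137 | 0.131 / 0.119 / 0.098 | 0.27 | ±0.08 / 0.13 / 0.19 |
| C | 0.194 | 0.185 / 0.168 / 0.138 | 0.38 | ±0.11 / 0.19 / 0.27 |

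The proportional gain is the same in all three; the absolute exposure is largest in C, the smallest comparison.

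**Effect on the CEAC (illustration).** Suppose the net benefit in comparison A is 0.15 SD, and read ρ as the correlation of net benefit with the baseline covariate. The probability of being cost-effective is Φ(0.15/SE). Unadjusted, Φ(0.15/0.129) = 0.88; adjusted, it is 0.89, 0.91 or 0.95.

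**Stratifiers.** Dynamic allocation balances locality and dyad relationship, so an analysis that ignores them overstates the SE by the factor 1/√(1 − R²), where R² is their share of the cost variance. For an assumed R² of 2%, 5% or 10% the excess is 1.0%, 2.6% or 5.4%.

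**The case against.** The strongest reply is that the article never calls the cost difference raw or unadjusted. The same sentence describes the MCS-12 effect as a mean difference, although the Effectiveness analysis section adjusts MCS-12 for baseline, so the phrase alone does not rule out adjustment. A condensed article may also leave covariates to a fuller plan that is not shown. This stands as far as it goes: one cannot say that the trial has excluded adjustment. But the article does more than stay silent. It sets out the estimator, the per-dyad formula and the resampling rule, and none of these steps has a place for baseline cost.

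The second reply is that nothing invalid follows. That stands in full. A reader might infer that the ICER is biased; it is not, because a randomised mean difference is unbiased and the bootstrap already reflects chance baseline imbalance. At ρ = 0.5, a one-standard-error imbalance in baseline cost moves comparison A by 0.065 SD, half of its standard error.

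Three further inferences are tempting and also go too far:

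- That the plan leaves chance imbalance in locality or dyad relationship. Allocation balances both, so only slight precision is at stake.
- That local costing of CSP and RYCT shows costs to differ by site. The text says only that items without a national unit cost are costed locally.
- That baseline costs are certainly available. The general data-collection schedule implies it, but no CSRI schedule is stated.

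Finally, regression on the two main effects alone would force additive costs on combined v TAU. Additivity is doubtful, since Carer Supporters in the combined arm are invited to RYCT sessions and receive extra training. The fix has to allow for that.

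**Conclusion.** The concern holds as a matter of efficiency, not validity. As described, the cost difference and the net benefit use follow-up cost with no baseline-cost term, out of step with the clinical analysis. The estimate is unbiased, but less precise than it could be, and it carries chance imbalance in baseline cost. The possible reduction in standard error is 5%, 13% or 29% at ρ = 0.3, 0.5 or 0.7. That range rests wholly on assumed correlations, and the documents offer no basis for choosing within it. Omitting locality and dyad relationship makes the spread only slightly too wide. The planned sensitivity analyses on costs and outcomes do not name covariate adjustment, so they do not settle the point.

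**What to change.** In Cost estimation, state that incremental cost, and net benefit at each λ, are estimated by regression on the four allocated groups (CSP, RYCT and their interaction), with baseline CSRI cost, locality and dyad relationship as covariates. Derive all three comparisons from this one model:

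- A and B as the stated margins. If groups are pooled at their allocated sizes, A weights CSP − TAU by 40/120 = 1/3 and combined − RYCT by 80/120 = 2/3. B weights RYCT − TAU and combined − CSP equally (80/160 of the RYCT side and 40/80 of the other side).
- C as combined v TAU, with no assumption of additive costs.

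Refit the model in each bootstrap replicate, still resampling within the four groups, and use the adjusted estimates in the ICER and CEAC for both the societal and the health and social care perspectives. Confirm that the CSRI is completed at baseline and state its recall period. If a fuller plan already adjusts costs, one sentence in the article saying so is enough.

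The cost is wording, the derivation of baseline CSRI costs and slightly more computation. No new data are needed if the CSRI is collected at baseline.

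### Net benefit is built from the change in MCS-12 with no baseline covariate named, while the effectiveness analysis adjusts for baseline: a modest, avoidable loss of precision and consistency

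*Protocol article*

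**What the plan says.** The article handles the MCS-12 effect in three places.

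- **Effectiveness analysis.** The estimator is a "multi-level analysis of covariance with outcome at 12 months after initial randomisation as dependent variable", with the outcome "at baseline and length of time on CSP as covariates".
- **Cost estimation, net benefit.** Each dyad's net benefit is λ × E − C, where "E is effectiveness, namely the change in the primary outcome". These values are bootstrapped "while keeping the four allocated groups at their original sizes". No covariate is named.
- **Cost estimation, ICER.** The mean cost difference is "divided by the mean difference between these groups in the MCS-12 over those 12 months". The text does not say whether this is a difference in change, in the 12-month score, or in an adjusted mean.

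The section Outcome estimation states what the economic and main analyses share: "The economic evaluation will employ the same procedures for calculating scores and imputing missing values as in the primary statistical analyses described above". That covers scoring and imputation, not the effect estimator. Under Secondary cost-effectiveness analyses, the QALY analyses are to follow the same stages as the primary economic ones.

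**The concern.** One primary outcome is given two estimators, and nothing in the article reconciles them. A change score removes baseline with a slope fixed at 1. When baseline and follow-up variances are equal, the best slope is the correlation r, which is below 1. The change score therefore over-corrects for chance baseline imbalance and is noisier than ANCOVA. Randomisation is stratified on locality and dyad relationship, and at the second stage on the first allocation, but not on baseline MCS-12. Chance imbalance on MCS-12 is therefore left to the analysis.

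Two things are at stake. The net-benefit comparison, and hence the CEAC, would carry more uncertainty than the data require. The effect implied by the economic analysis could also differ from the trial's own effect estimate. The second matters most when the true effect is near zero, because the interpretation rules under Cost estimation turn on whether an intervention is more or less effective.

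**Working it through.** **Plan's own figure.** The article states no precision for the ICER, net benefit or CEAC, so there is none to reproduce. The group sizes follow from Sample size and Design: 240 completed dyads at 1:2:1:2 give 40 (TAU), 80 (RYCT), 40 (CSP) and 80 (combined). The CSP margin is 120 v 120. With an effect of 0.42 SD, two-sided 5% and no baseline adjustment, power there is 90.2%, which agrees with the stated figure of more than 90% for CSP.

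**Inputs**

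- Planned CSP effect: 0.42 SD (Sample size).
- Baseline to 12-month correlation r: not given, so assumed at 0.3 to 0.74. The upper end borrows the MCS-12 reliability of 0.74 (Primary outcome).
- Ratio k = Var(cost) / (λ² × Var(MCS-12)): not given, so assumed at 1 and 4, with cost independent of outcome.

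**Step 1: MCS-12 alone.** With unit variances, Var(change) = 2(1 − r) and Var(ANCOVA) = 1 − r², so the ratio is 2/(1 + r).

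| r | Var(change) | Var(ANCOVA) | Variance ratio | SE ratio | 240 dyads worth |
|---|---|---|---|---|---|
| 0.3 | 1.40 | 0.91 | 1.54 | 1.24 | 156 |
| 0.5 | 1.00 | 0.75 | 1.33 | 1.15 | 180 |
| 0.74 | 0.52 | 0.452 | 1.15 | 1.07 | 209 |

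Simulating 20,000 trials at r = 0.5 and 120 v 120, with a true effect of 0.42, gave means of 0.418 (change) and 0.419 (ANCOVA), so neither is biased. The standard errors were 0.129 and 0.112.

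**Step 2: net benefit.** Cost variance enters both versions, so SE ratio = √[(2(1 − r) + k) / (1 − r² + k)].

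| r | k = 1 | k = 4 |
|---|---|---|
| 0.3 | √(2.40/1.91) = 1.12 | √(5.40/4.91) = 1.05 |
| 0.5 | √(2.00/1.75) = 1.07 | √(5.00/4.75) = 1.03 |
| 0.74 | √(1.52/1.452) = 1.02 | √(4.52/4.452) = 1.01 |

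The penalty is about 2% to 12% at k = 1 and 1% to 5% at k = 4. As λ rises, k falls and the penalty moves towards the step 1 figures.

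**Step 3: disagreement between the two estimates.** They differ by (1 − r) times the chance baseline difference between groups. Take a typical difference, meaning one standard deviation of its sampling distribution, at r = 0.5.

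- CSP margin: √(1/120 + 1/120) = 0.129, and 0.5 × 0.129 = 0.065 SD. As a share of 0.42 this is 0.065/0.42 = 15%.
- Combined v TAU: √(1/80 + 1/40) = 0.194, and 0.5 × 0.194 = 0.097 SD.

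The simulated SD of the difference at the CSP margin was also 0.065. The two estimates took opposite signs in 0.06% of trials at a true effect of 0.42, and in about 17% at a true effect of zero.

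**The case against.** The best reply is that E defines what each dyad contributes, not how groups are compared. Once baseline MCS-12 is a linear covariate, regressing change on allocation gives the same treatment coefficient as regressing the 12-month score, and this carries over to λ × change − cost. The choice of change does no harm in itself. The loss arises only if no covariate is used, and a fuller economic plan may name one. The article also promises sensitivity analyses: "We shall conduct sensitivity analyses to explore the effect on conclusions of varying key assumptions about costs and outcomes".

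The algebra is right, and it shows how small the repair is. It does not remove the point. The article sets out a procedure (per-dyad net benefit, then a bootstrap within the four groups), and following it as written gives the less precise comparison. The general promise of sensitivity analyses does not set the main estimator.

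Four stronger readings are tempting, but the article does not support them.

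- *The ICER itself is computed from unadjusted change.* E appears only in the net-benefit formula. The ICER is defined separately and the text is silent on its form, so this would be inference.
- *The CEAC loses the full MCS-12 penalty.* Cost variance dilutes it, as step 2 shows. Any statement about the CEAC also presumes that it is built from incremental differences between groups. The article instead speaks of the proportion of dyads with positive net benefit, which is a separate matter.
- *The disagreement is about a quarter of the planned effect.* That would set the combined v TAU shift of 0.097 against 0.42, which is the CSP effect and belongs to the 120 v 120 margin. The like-for-like figure is 15%.
- *The economic analysis is biased.* Under randomisation it is not.

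**Conclusion.** The point holds as a modest one about precision and consistency. The article's net-benefit procedure compares changes in MCS-12 without a stated baseline covariate, while its effectiveness analysis adjusts for baseline. For r between 0.3 and 0.74, the standard error for MCS-12 is 24% to 7% larger than it need be. For net benefit the excess is roughly 1% to 12% under the assumed cost-variance ratios. A typical chance imbalance at r = 0.5 separates the two estimates by about 0.065 SD for CSP and 0.10 SD for combined v TAU.

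These sizes rest on the assumed r, equal variances at baseline and 12 months, cost independent of outcome, and k of 1 to 4. The article fixes none of these. The direction does not depend on them beyond equal variances and r below 1. No conclusion of the trial is invalidated. The undefined ICER denominator is a gap to close in the same edit, not evidence that the ICER is wrong.

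**What to change.** State that, within each bootstrap replicate, net benefit (or 12-month MCS-12 and cost separately) is regressed on:

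- the allocation factors, with the contrast that matches each of the three economic comparisons;
- baseline MCS-12;
- baseline cost, where the CSRI provides it;
- the stratifiers, locality and dyad relationship.

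Use the adjusted incremental differences for both the ICER denominator and the CEAC, and say so where the ICER is defined. For the QALY analyses, adjust for baseline EQ-5D in the same way.

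Do not copy the effectiveness model whole. Length of time on CSP arises after randomisation and is tied to CSP allocation, so including it could distort the CSP effect and add another source of disagreement.

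The cost is a few sentences and one regression step inside a bootstrap that is already planned. Baseline data are already collected before randomisation, so no new data are needed.
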